**Method:**

This study is a randomized controlled trial that follows a parallel design. Consenting pregnant women in their second trimester (between 12^th^ and 20^th^ week gestation) will be randomly assigned to an intervention group (GMBPMI) or a control group (psychoeducation). The intended sample size is 198, with 99 participants in each group. Three levels of outcomes will be measured at baseline, post intervention in both the intervention and control groups, and at 36-week gestation and five-week postpartum. The primary outcomes include maternal psychological stress, mindfulness and positive appraisal HRV. Secondary outcomes are psychological and physical wellbeing. Tertiary outcomes include obstetric and neonatal outcomes, and social support. Analyses will follow an intention-to-treat method and repeated measures MANOVA will be conducted to compare changes in primary and secondary outcomes. A series of mixed-effects models will be fitted to assess the mediation effects.

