### Sample size calculation

The previous eastern-based meditation intervention (EBMI) study reported an effect size of 0.44 in reducing prenatal distress and an attrition rate of around 20% [28]. In the proposed study we assume an overall moderate effect size of 0.4 and a conservative attrition rate of 25%. Setting a power at 90%, a significance level of *p* < .008 (corrected for six primary outcomes), a sample size of 99 per arm is needed for a two-arm repeated measures design (GPower, version 3.1). Thus, the targeted total sample size is 198. Considering this is a web-based intervention, we will consider expanding the sample size to ensure enough statistical power after preliminary data analysis.

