### Four hypotheses

The intervention group would show a greater increase in maternal mindfulness and positive appraisal than the control group at T1, T2 and T3.The intervention group would show a greater reduction in stress and depression than the control group at T1, T2 and T3 and these outcomes would be mediated by the enhancement in positive appraisal.The intervention group would show a greater increase in HRV than the control group at T1, T2 and T3 and these outcomes would be mediated by the reduction in stress and depression.The levels of stress and depression would be negatively associated with obstetric and neonatal outcomes at T3 and these correlations would be mediated by HRV.

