### Data analysis

Quantitative data including scale measures and the HRV index will be collected at four time-points as articulated above.

Intention-to-treat analysis will be performed and missing data due to drop–out will be handled by the ‘multiple imputation’ technique [51]. 1) Using a two-arm RCT design, the efficacy of the intervention will be examined by repeated measures MANOVA on both the primary and secondary outcome variables, while adjusting for individual factors. Partial eta-squared values will be calculated to measure the effect size; values of .02, .13 and .26 suggest small, medium, and large effect sizes, respectively [52]. 2) To investigate the within-group effect, serial trend analysis from T0 to T3 will be conducted on the primary and secondary outcome variables. 3) A series of linear mixed-effects models will be fitted to assess the mediation effects. 4) The software Elite HRV Team Dashboard will be used for HRV data collection. Three HRV indexes will be computed for analysis, namely RMSSD (Mean squared difference between consecutive normal-to-normal intervals), SDNN (standard deviation of beat-to-beat intervals) and HF (absolute power of HF band).

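### The protocol names a MANOVA over primary and secondary variables as its only between-arm test, which as a joint test answers neither the outcome-specific hypotheses nor the alpha of .008

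*Protocol article*

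**What the plan says.** All places are in the protocol article.

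- **Sample size calculation:** the significance level is .008, "corrected for six primary outcomes", with 90% power, an effect size of 0.4, 25% attrition and 99 women per arm.
- **Four hypotheses:** hypothesis 1 concerns mindfulness and positive appraisal. Hypothesis 2 begins "The intervention group would show a greater reduction in stress and depression than the control group". Hypothesis 3 concerns HRV. Each refers to T1, T2 and T3.
- **Data analysis:** efficacy is to be examined by "repeated measures MANOVA on both the primary and secondary outcome variables, while adjusting for individual factors", with partial eta-squared values as the effect size. This section does not mention .008.
- **Abstract, Method:** "repeated measures MANOVA will be conducted to compare changes in primary and secondary outcomes".
- **Introduction:** the first listed aim is the effect on psychological distress.
- **Table 1:** there are seven primary rows: general stress, pregnancy-specific stress, depression, state mindfulness, daily mindfulness, coping and HRV. Pregnancy-specific stress and coping are not measured at T3, and daily mindfulness is measured weekly.

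**The concern.** The three sections do not describe the same confirmatory analysis. A Bonferroni level for six outcomes makes sense only if six tests are run and each is judged at that level. Hypotheses about named outcomes likewise need a result for each outcome. A MANOVA on the primary and secondary variables together gives a single test of a different null, that the arms differ on none of the variables. It is the only between-arm test that the article names.

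If that joint test is what is run, a significant result says that something differs between the arms. It does not say what. The difference could lie in mindfulness, which is the skill the programme trains, or in a secondary scale. The question about distress would be open, and the .008 would have no test to which it belongs.

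**Working it through.** **1. The alpha.** .05/6 = .0083, so .008 is a rounded-down Bonferroni level for six tests. Six tests at .008 have a familywise error of at most 6 × .008 = 4.8%, or 1 − .992^6 = 4.7% if they are independent. The level therefore fits six separate tests and does nothing for one joint test. With the seven primary rows of Table 1, the bound is 7 × .008 = 5.6%, and .05/7 = .0071.

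**2. What a joint test does when only mindfulness moves.** The documents give no correlations, so these are assumptions:

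- K = 11 outcomes: the six in the correction, plus five secondary scales (anxiety, positive affect, negative affect, spirituality, stagnation).
- Three changes from T0 for each outcome, giving p = 33 variables. This simplifies Table 1, where two primary scales have no T3.
- Visit correlation .5; common outcome correlation ρ of .2 or .4.
- The same shift d at each visit for mindfulness, and none on any other outcome. The 0.4 is the planning value; 0.6 is assumed.
- Alpha .008; n = 99 per arm, or 74 after 25% attrition (99 × .75 = 74.25).

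The test is Hotelling's T-squared. Its F form has p and 2n − p − 1 degrees of freedom, here 33 and 198 − 33 − 1 = 164. The noncentrality is

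λ = (n/2) × d² × a × b.

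- a comes from the visits. With unit outcome variance, each change has variance 2(1 − .5) = 1 and each pair has covariance .5, so a = 3/(1 + 2 × .5) = 1.5.
- b is the diagonal element of the inverse outcome correlation matrix, b = [1 + (K − 2)ρ] / {(1 − ρ)[1 + (K − 1)ρ]}. For ρ = .2 it is 2.8/(.8 × 3) = 1.167. For ρ = .4 it is 4.6/(.6 × 5) = 1.533.

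The extremes at 99 per arm are:

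- d = 0.4, ρ = .2: λ = 49.5 × .16 × 1.5 × 1.167 = 13.9.
- d = 0.6, ρ = .4: λ = 49.5 × .36 × 1.5 × 1.533 = 41.0.

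Probability that the joint null is rejected:

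| True d on mindfulness only | ρ | 99 per arm | 74 per arm |
|---|---|---|---|
| 0.4 | .2 | 15% | 8% |
| 0.4 | .4 | 25% | 13% |
| 0.6 | .2 | 59% | 34% |
| 0.6 | .4 | 80% | 53% |

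**3. A second set-up.** A simulation used one time-point, 12 variables (seven primary, five secondary), pairwise correlation .3, d = 0.4 on mindfulness only and 99 per arm, with 4,000 runs. The joint test rejected in about 23% of trials at .008 and 49% at .05. A separate test at .008 on a scale that did not move rejected in about 0.8%.

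The rates depend on the assumed correlations and effect. Both set-ups show the same thing: the joint test often rejects with no effect on distress, and separate tests keep their nominal level on the distress scales.

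**The case against.** **The per-outcome reading.** Repeated measures MANOVA is also the usual name for the multivariate treatment of time within one outcome, run on each variable in turn. Several details fit that: the alpha divided by six, the G*Power repeated-measures calculation, and eta-squared values in the plural. The unequal schedules in Table 1 also make one model over all outcomes and visits hard to fit. This objection stands in part. The joint reading is the natural one but is not certain. The other is nowhere written, and nothing ties .008 to the MANOVA.

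**Follow-up tests.** Univariate tests after a MANOVA may sit in an analysis plan that is not shown, so their absence from an article is no defect in itself. The point rests on the test that the article does name, which does not match its alpha or its hypotheses.

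**Mindfulness reported as efficacy on distress.** A reader might infer that a gain in mindfulness alone will be claimed as a benefit for distress. No such rule is written, and the hypotheses tie mindfulness to hypothesis 1 and stress and depression to hypothesis 2.

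**Inflated error.** A reader might set the 15% to 80% against .008 as a type I error. That would be wrong. Mindfulness truly moves in those scenarios, so rejecting the joint null is correct. What fails is the ability to say which outcome moved.

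**Lost power.** A reader might also expect the joint test to miss a real effect on all outcomes. Like for like, with d = 0.4 on all 11 outcomes, alpha .008 and 99 per arm, this does not hold generally. For unadjusted changes at three visits, a single-outcome test has 60% power and the joint test 46% at outcome correlation .4, but 84% for the joint test at .2. For baseline-adjusted T1 to T3 means at correlation .4, the figures are 95% and 98%. No claim of lost power is made.

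**Conclusion.** The concern holds as a mismatch between sections. The article fixes a per-outcome alpha and outcome-specific hypotheses, then names a between-arm test that, read as one joint model, can use neither. It does not say which reading is meant. Under the joint reading, a significant result does not identify stress or depression. The 15% to 80% range at 99 per arm illustrates how often that could arise when only mindfulness moves. It rests on assumed correlations, an assumed effect of up to d = 0.6 and a simplified visit schedule. Under the per-outcome reading the problem is one of unclear wording, and the same correction cures it. Separately, the six outcomes in the correction do not match the seven primary rows in Table 1.

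**What to change.** In Data analysis, and correspondingly in the Abstract, state that:

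1. the between-arm repeated-measures test is run separately for each primary outcome at the corrected alpha;
2. hypothesis 1 is judged only on mindfulness and positive appraisal, the between-arm part of hypothesis 2 only on stress and depression, and that of hypothesis 3 only on HRV;
3. secondary outcomes are analysed separately and are supportive;
4. any joint MANOVA is descriptive.

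Also list the primary outcomes that the correction counts, and reconcile the six with the seven rows of Table 1. If all seven are kept as primary, the level becomes .05/7 = .0071.

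This changes wording only and needs no new data or participants. The small downside is several results in place of one overall p-value.

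### Partial eta-squared is read on one fixed set of cut-offs without saying which test it belongs to; taken from a multivariate test, it is liable to overstate the benefit

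*Protocol article*

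**What the plan says.** The Data analysis section of the protocol article states that "the efficacy of the intervention will be examined by repeated measures MANOVA on both the primary and secondary outcome variables, while adjusting for individual factors". The next sentence gives the effect size: "Partial eta-squared values will be calculated to measure the effect size; values of .02, .13 and .26 suggest small, medium, and large effect sizes". The section names no bias-corrected version. It also does not say whether all outcomes enter one MANOVA, whether primary and secondary outcomes are modelled separately, or whether the value is reported for a multivariate test or outcome by outcome.

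On missing data, the same section says that "missing data due to drop–out will be handled by the ‘multiple imputation’ technique", under intention to treat. The Sample size calculation section gives the number randomised ("a sample size of 99 per arm is needed for a two-arm repeated measures design (GPower, version 3.1") and the significance level ("Setting a power at 90%, a significance level of *p* < .008 (corrected for six primary outcomes").

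**The concern.** Partial eta-squared is a sample proportion of variance explained and cannot be negative, so it is biased upwards. In a multivariate test the bias grows with every outcome and visit added, whatever the treatment does. A single set of cut-offs cannot mean the same thing for one scale over time as for a family of scales over time.

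The label matters because readers will take it as the size of the programme's benefit. The Discussion section plans publication and promotion of the programme to clinics and hospitals. If a word such as medium mainly reflects how many scales were entered, it says little about what a participant gains.

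**Working it through.** **Inputs.** N = 198 comes from the Sample size calculation section. It is the main case because dropouts are to be imputed. The article prints no expected partial eta-squared, so there is no figure of its own to reproduce on this point. The number of contrasts p is counted from Table 1 as changes from T0, leaving out the weekly daily-mindfulness scale:

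- Primary: perceived stress 3, prenatal distress 2 (not measured at T3), depression 3, five-facet mindfulness 3, coping 2 (not measured at T3), HRV 3. The sum is 16. Six outcomes at three contrasts each would give 18.
- Secondary: anxiety, positive affect, negative affect, spirituality and stagnation, 5 × 3 = 15.
- Joint: the nine measures taken at all four visits give 9 × 3 = 27; all eleven give 16 + 15 = 31; replacing one HRV score by the three indexes in the Data analysis section adds 6, giving 37.

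**Formula.** With two arms, multivariate partial eta-squared is V = 1 − Wilks' lambda. With no effect and no covariates, V follows a Beta(p/2, (N−1−p)/2) distribution with mean p/(N−1). The smallest value significant at .05 is the 95th percentile of that distribution.

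**Results at N = 198, no treatment effect:**

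| Test | p | Mean = p/197 | P(V ≥ .13) | Smallest V significant at .05 |
|---|---|---|---|---|
| One outcome over time | 3 | .015 | about 0 | .039 |
| Secondary family | 15 | .076 | 4% | .124 |
| Primary family | 16 | .081 | 5% | .131 |
| Primary family, upper count | 18 | .091 | 10% | .143 |
| Joint, nine measures | 27 | .137 | 55% | .198 |
| Joint, eleven measures | 31 | .157 | 76% | .221 |
| Joint, three HRV indexes | 37 | .188 | 94% | .256 |

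The no-effect mean reaches .13 when p is at least .13 × 197 = 25.6, that is, 26 contrasts in one test. Simulation at N = 198 agreed with the formula: .016 for p = 3, .092 for p = 18 and .167 for p = 33.

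**The same true effect under different p.** A true standardised distance of 0.4 has population partial eta-squared 0.16/4.16 = .038, which is small on the article's cut-offs. The expected sample value at N = 198 is .043 for p = 1, .053 for p = 3, .126 for p = 18 and .199 for p = 33. The last is labelled medium, although the effect has not changed.

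**Sensitivity.** With 12 covariates (an assumed number) the joint means for 27 to 37 contrasts become .146 to .200. In a completer analysis with 25% attrition (N = 148), which is not the planned analysis, they would be .184 to .252.

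**Effect of a correction.** Adjusting for degrees of freedom, 1 − (1 − V)(N−1)/(N−1−p), gives exactly 0 at the no-effect mean V = p/(N−1), whatever p is.

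**The case against.** The strongest reply is that the article never commits to one large joint test. The significance level corrected for six primary outcomes points to outcome-level tests, and the hypotheses are framed by construct. Prenatal distress and coping stop at T2, so a standard four-visit MANOVA cannot hold every measure. At outcome level the no-effect mean is .015, below the small cut-off, and the smallest value significant at .05 is .039, labelled small. All eleven measures on the common T0 to T2 visits (22 contrasts) have a mean of 22/197 = .112, still small. This stands. A reader might infer that noise averages medium under this plan. That needs about 26 or more contrasts in one test, which the text permits but does not fix.

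A reader might also infer that the published benefit will certainly be overstated. The documents do not support that either. At outcome level the labels can err the other way: the planning figure of 0.4, called moderate in the Sample size calculation section, is a partial eta-squared of .038, labelled small, if it is a standardised mean difference. If it is Cohen's f, it is 0.16/1.16 = .138, labelled medium. The article does not state the metric.

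It is also fair to say that the F test accounts for degrees of freedom, so false positives are not inflated, and that most no-effect values above .13 in the joint test would be non-significant. The significance filter does not rescue the label, however. In the primary family every significant value is already at least .131. For the secondary family the threshold is .124, just under the cut-off.

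Finally, the article is condensed, and an unseen analysis plan may add mean differences with confidence intervals. Their absence is therefore not the point. The point is the effect size and cut-offs that the article does state.

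**Conclusion.** The concern holds conditionally. The article fixes an upward-biased statistic and one set of labels without naming the test. At N = 198 the no-effect mean runs from about .015 (one outcome) through .08 to .09 (primary family) to .14 to .19 (joint test), which takes it from below small to medium on the same scale. A significant primary-family multivariate result would be labelled at least medium regardless of its true size. Overstatement is therefore a real risk if the reported value is multivariate. It does not apply to outcome-level values, and significance testing is unaffected.

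The figures assume the contrast counts taken from Table 1, no covariates in the main case, and the complete-data distribution as an approximation for multiply imputed data. The number of contrasts is an assumption because the article does not specify the model.

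**What to change.** In the Data analysis section, replace the partial eta-squared sentence. For each primary and secondary outcome, report the adjusted between-arm difference in scale points at each visit where it is measured (T1, T2 and, where scheduled, T3) with a 95% confidence interval, plus a standardised mean difference. If a variance-explained figure is kept, name the test it belongs to, use a bias-corrected version (omega- or epsilon-squared) per outcome, and attach no small, medium or large label to a multivariate value.

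The cost is one or two sentences and a little more routine output. Effect-size labels may look less favourable. The change can be made before analysis and needs no new data.

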### Data monitoring

Considering the timeframe and the minimal risk known to the participants of the current study, the Data Monitoring Committee was not formed [53]. The research team will continue monitoring the needs of forming such team.

### Strategies for improving adherence

Participants will be requested to take an HRV measure after everyday mindfulness practice. The measurements will be collected through a computer software Elite HRV Team Dashboard, allowing the research assistant (RA) to track the adherence of each participant. For those participants who failed to practice mindfulness, the RA will send a reminder through WhatsApp.

### Trial status and timeline

The tentative schedule of the research is shown in the Figs 2 and S1. As of 15 April 2021, the study team is preparing the research materials, with recruitment expected to start in May. Intervention and data collection is expected to be completed by May 2022. Data analysis and report writing will be completed by the end of December 2022. Any amendment or deviation from the protocol will be reported to the Human Research Ethics Committee at the University of Hong Kong by submitting an application for amendment of an approved project form in hardcopy.

**Fig 2 pone.0270683.g002:**
[figure not shown]
SPIRIT schedule of enrolment, intervention and assessments. Note: -t1, 0, baseline; t1, post 8-week intervention; t2, 36-week gestation follow up; t3. 5-week postpartum follow up.

## Discussion

The study’s objective is to test the efficacy of GMBPMI in improving mindfulness and positive appraisal, and reducing pregnant related stress and depression. As a possible mediator, HRV will also be examined to confirm the efficacy of GMBPMI on ANS changed among pregnant women. Additionally, trajectory of maternal psychological distress will also be examined in relation to obstetric and neonatal outcomes at 5-week postpartum period. In line with the research objectives, the primary outcomes of the research are changes in maternal psychological distress, mindfulness, positive appraisal and the HRV index. The secondary outcomes are general psychological and physical wellbeing, such as anxiety, affect, spirituality and stagnation. The clinical outcomes include obstetric and neonatal outcomes, such as gestational age at birth, pregnancy complications, mode of birth, infant Apgar score and head circumference.

This study has both strengths and limitations. Strengths include the randomized controlled trial study design with a large sample size of 198 to ensure sufficient power to demonstrate the efficacy of GMBPMI intervention. More importantly, the research stands out in its innovative delivery mode. Delivered through mobile devices, this study is an extension of the previous face-to-face EMBI intervention, making it feasible for pregnant women to practice at home. Furthermore, this study is one of the few research projects to examine not only psychological but also physiological changes (e.g., HRV), allowing us to detect the potential mediation effect of HRV on GMBPMI and psychological wellbeing. A limitation of this study is that participants in the control group might seek other services or interventions similar to MBI to improve their psychological wellbeing, potentially leading to difficulties in detecting the group difference. To deal with such contamination, we will collect data of any alternative treatments the participants are taking.

A significant part of the current study is that the results of the research (reducing maternal psychological distress by GMBPMI) are to be disseminated not only in Hong Kong SAR but also internationally. Hence, we propose the following approach: Upon completion of the study, our research team will seek to publish the data output in international peer reviewed scientific journals, as well as disseminating the results through presentations at local and international conferences. The research material will be further refined by reflecting on the obstacles during the intervention procedure. A guideline booklet will be generated for the general public to use. Furthermore, with the success of this research, it is expected that the whole program will be promoted through the hospital authority to private clinics and public hospitals as supportive resources for pregnant women. All the materials are expected to be accessed through online platforms either on the Department of Health website by the government of the Hong Kong Special Administrative Region Family Health Service—Home (fhs.gov.hk), or through a privately created webpage by the research team.
